### Interventions

2.3

Control group: The control group will be given conventional treatment to regulate blood pressure, blood glucose, and blood lipid. At the same time, drugs such as nutritional nerves, promoting blood circulation, and removing blood stasis are used, adjusted according to the needs of the disease, and routine rehabilitation training is performed.

Intervention group: This group of patients will be given acupuncture combined with rehabilitation training. TCM acupuncture therapy: Acupoints include *Quchi*, *Waiguan*, *Hegu*, *Dicang*, *Sanyinjiao*, and *Zusanli*. The twisting technique will be used, leaving the needles for 30 min, and treated once a day for 2 weeks. Rehabilitation training is first of all passive activities. With the help of ropes, sticks and other tools, fists, leg lifts, cross fingers, etc are performed 3 times a day for 30 min each time. When the muscle strength returns to level 3, take active training, including voluntary turning, sitting exercises, standing exercises, walking training, etc. The total application time will be 8 weeks. At the same time, closely monitor the change of the condition in order to control the deterioration of the condition in time.

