## Abstract

**Introduction::**

Erectile dysfunction refers to the continued inability of the penis to reach and maintain sufficient erections to achieve a satisfactory sex life and last at least 6 months. As part of traditional Chinese medicine, acupuncture has been widely used in clinical practice. In order to evaluate, the exact effect of acupuncture on the clinical efficacy of patients with Post-stroke Erectile dysfunction (PSED), this experiment uses randomized controlled experiments.

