**Methods/design::**

This pragmatic randomized controlled trial will recruit 103 patients who are diagnosed with PSED. Simple randomization to conventional treatment with a 1:1 allocation ratio will be used. Ten 30-min acupuncture sessions will be provided to patients assigned to the Intervention group. All participants will continue to receive conventional treatment. The selection of outcomes will be evaluated by International Erectile Function Index-5 (IIEF-5) score at week 8.

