Based on the current needs of patients with Post-stroke Erectile dysfunction (PSED) that do not respond well to conventional treatments, and the need for clinical research on the level of evidence for efficacy, it is worthwhile to further explore the treatment model of acupuncture for PSED. Therefore, we will evaluate the clinical effectiveness and safety of acupuncture in the diagnosis and treatment of PSED. We hope that the results of this study will provide clinicians with acupuncture treatment for PSED and more treatment options.

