#### Conditions for participants to suspend and withdraw from the clinical trial

2.2.4

Researchers participating in clinical trials should carefully record the reasons for the suspension of the trial and the relationship with the clinical trial. It is necessary to clearly record the unwillingness of the subjects to continue the clinical trials, put forward the reasons for withdrawing from the clinical trials, and record the evaluation indicators at the time of discontinuation in detail.

1.Those who cannot adhere to treatment;2.Allergic reactions or serious adverse reactions during the test, the test should be suspended:3.Those who have not been treated strictly according to the plan;4.People who withdrew from the study on their own

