The factors that affect the sexual function of stroke patients are many and complex. Stroke location, area, disease occurrence and development process may affect patients’ sexual function. Therefore, this study made strict rules on case selection, excluding patients who could not take care of themselves and had emotional cognition disorders; when selecting cases, patients had a recent stroke >3 months to ensure that the stroke was stable and chose to comply as much as possible Patients with better sexuality and cooperation should conduct a questionnaire study to reduce the impact of other factors on the patient's sexual function.^[16]^ The manifestation of sexual dysfunction in young and middle-aged male patients is mainly ED. In sexual activity, men are often active acquirers, and the occurrence of ED is determined by multiple factors. Studies have shown that the high-risk factors that affect men's erections are mainly related to patients’ smoking history, high blood pressure, worries about recurrence of stroke, and daily antihypertensive receptor inhibitors. The possible reasons are:

1.the influence of subjective assessment of husband and wife relationship. Due to privacy and the personality of Chinese people, most respondents are unwilling to proactively expose their rapport with their spouse, affecting the final statistics.2.Most studies have shown that emotional instability in patients can affect sexual quality of life.

After excluding those cases with depression and anxiety, they found that abnormal changes in mood can significantly affect the quality of sexual life of patients.^[17]^ Further interviews with patients showed that some patients had misunderstandings and even fears about normal sexual life, and worried that intense sexual life would increase the risk of stroke. This misunderstanding is completely unnecessary, which further confirms the lack of clinical related guidance and deserves further attention in the clinic. Therefore, we will evaluate the clinical effectiveness and safety of acupuncture in the treatment of PSED. We hope that the results of this study will provide clinicians with the basis for acupuncture treatment of PSED and more treatment options.

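### The abstract gives conventional treatment to everyone, but section 2.3 names the conventional drugs for the control group only; followed literally, 2.3 would not let a difference be attributed to acupuncture

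*Protocol article*

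**What the plan says.** The abstract (Methods/design) describes acupuncture for the intervention group on a common background: "All participants will continue to receive conventional treatment".

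Section 2.3 Interventions describes the arms separately.

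- **Control group:** "The control group will be given conventional treatment to regulate blood pressure, blood glucose, and blood lipid". Drugs for nerve nutrition, circulation and blood stasis are added as needed, and "routine rehabilitation training is performed".
- **Intervention group:** "This group of patients will be given acupuncture combined with rehabilitation training". The acupuncture points and schedule follow, then a specified rehabilitation programme: passive exercises three times a day for 30 minutes each, moving to active training as muscle strength returns. No conventional drug is mentioned.

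The stated question concerns acupuncture itself. The abstract (Introduction) speaks of "the exact effect of acupuncture on the clinical efficacy of patients", and section 1 says "we will evaluate the clinical effectiveness and safety of acupuncture in the diagnosis and treatment of PSED".

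**The concern.** The two descriptions imply different treatment contrasts. Under the abstract, acupuncture is added to care that both arms share, so the comparison addresses the stated question. Under a literal reading of 2.3, acupuncture plus rehabilitation is compared with drugs plus rehabilitation. A difference in the IIEF-5 effective rate would then mix the gain from acupuncture with the effect of not having the drugs, and no analysis of two arms could separate them.

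The article gives some reason to think the background treatment bears on the outcome. Section 3 (Discussion) names, among the main factors affecting erection, "high blood pressure, worries about recurrence of stroke, and daily antihypertensive receptor inhibitors". That suggests an effect in either direction is possible, but it does not establish one.

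Conduct is affected too. Section 2.2.4 lists among its conditions for suspension and withdrawal: "Those who have not been treated strictly according to the plan". An intervention patient not receiving the drugs is on plan by section 2.3 and off plan by the abstract. By section 2.6, the physiotherapists and patients know the allocation when either reading is applied.

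**Working it through.** **1. Components named for each arm**

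| Component | Abstract: control | Abstract: intervention | 2.3: control | 2.3: intervention |
|---|---|---|---|---|
| Conventional drugs | yes | yes | yes | not named |
| Rehabilitation | not mentioned | not mentioned | yes, described as routine | yes, programme specified |
| Acupuncture | no | yes | no | yes |

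Section 2.3 names six drug purposes for control (blood pressure, glucose, lipids, nerve nutrition, circulation, stasis) and none of the six for intervention. Rehabilitation is the only component named in both arms. The count describes the wording; it is not evidence of an effect.

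**2. What the comparison estimates.** Assume additive effects on the effective rate: A for acupuncture, D for the drugs, and R for any difference in rehabilitation (intervention minus control).

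- Abstract: difference = A + R. If the programmes are the same, R = 0 and the difference is A.
- Section 2.3 read literally: difference = A − D + R. Even with R = 0, one observed difference cannot yield both A and D.

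**3. Planned difference.** Section 2.5 assumes 0.80 and 0.50, a difference of 0.30. These rates reproduce the 48 per group: 10.5 × (0.8 × 0.2 + 0.5 × 0.5) ÷ 0.3² = 47.83, rounded up to 48. (The substitution printed in 2.5 uses other numbers; that is a separate matter.) The 48 is the same under either reading, so the sample size does not settle which contrast is meant.

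**4. Scale, on an assumed D.** The documents give no value for D, so these are illustrations only.

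- |D| = 0: 0 of the planned difference.
- |D| = 0.05: 0.05 ÷ 0.30 = 0.17 of it.
- |D| = 0.10: 0.10 ÷ 0.30 = 0.33 of it.

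With A = 0.30, R = 0 and the literal reading, D = +0.10 (drugs help) gives an expected difference of 0.30 − 0.10 = 0.20, and D = −0.10 (drugs impair) gives 0.30 + 0.10 = 0.40.

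The normal approximation for two proportions (pooled variance under the null, two-sided 0.05, 48 analysed per group) gives these probabilities of a significant result in favour of the intervention group:

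| Assumed case | Control rate | Intervention rate | Probability |
|---|---|---|---|
| As planned | 0.50 | 0.80 | 0.88 |
| A = 0.30, D = +0.10, drugs in control only | 0.50 | 0.70 | 0.52 |
| A = 0, D = −0.10, drugs in control only | 0.50 | 0.60 | 0.16 |
| A = 0, D = 0 | 0.50 | 0.50 | 0.025 |

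A drug imbalance could therefore hide an acupuncture effect or produce an apparent one, depending on a sign the documents do not give.

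**The case against.** The strongest reply is that this is an omission, not a contradiction. The abstract is explicit and covers both arms, its wording implies that patients are already on conventional treatment, and it calls the trial pragmatic. Section 1 motivates the trial by patients who respond poorly to conventional treatment, which suits an add-on design. Nothing says drugs are stopped, and leaving half of a post-stroke sample without blood pressure, glucose and lipid control would be implausible. A condensed article may describe a shared rehabilitation programme only once, and the missing flow chart may show the arms correctly.

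Much of this stands. Add-on is the likely intent. The component count and the assumed range for D carry no evidential weight. The link to section 3 is loose: it is a list of risk factors from other studies, it names one type of antihypertensive, and section 2.3 names no drug class.

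It does not remove the point. Section 2.3 is the section from which treatment is delivered. If shared care had simply been left unsaid there, rehabilitation would have been left unsaid as well; instead it is restated in detail for the intervention arm and the drugs are not. Control rehabilitation is called routine while the other arm has a fixed schedule, and no sentence equates them. Condensation can excuse missing detail, but here one document gives two descriptions of what an arm receives, and the shown text does not reconcile them.

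**Conclusion.** The concern holds, and it should be fixed before the trial starts. The abstract and section 2.3 describe different contrasts, and 2.3 also leaves it unsettled whether rehabilitation is the same in both groups. The consequence is conditional: only if 2.3 is followed literally do the arms differ in drugs as well as acupuncture, and then a difference in effective rate cannot be attributed to acupuncture. If the abstract is followed and rehabilitation is the same, the design answers its question and only the wording needs repair.

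No direction or size of bias can be derived. The figure of up to one third of the planned 0.30 rests on additive effects and an assumed drug effect of at most 0.10, and serves only for scale. Confidence is high that the text is unreconciled; it is not a claim that drugs will be withheld.

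**What to change.** State in section 2.3 that both groups receive the same conventional drug treatment, adjusted by the same rules, and the same rehabilitation programme, and that acupuncture is the only planned difference. Record concomitant drugs by arm, if the case report form does not already do so, so that balance can be checked.

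If the arms are meant to differ, correct the abstract instead and restate the objective and conclusions as a comparison of two treatment packages. Which design is right is a clinical matter for the investigators.

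The cost is one or two sentences and perhaps one form field. Section 4 says recruitment has not started and section 2.9 says ethics submission is still to come, so the change disturbs no data and leaves the sample size as it is.

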### Outcome measures

2.4

#### Primary outcome measures

2.4.1

We will use the International Erectile Function Index-5 (IIEF-5) as the main outcome indicator.

1.Recovery: IIEF-5 score ≥22 points after treatment2.Significant effect: IIEF-5 score < 22 points after treatment, points improved ≥60%;3.Effective: IIEF-5 points <22 points after treatment. The improvement of points is between 30% and 60%;4.Ineffective: IIEF-5 points after treatment are <22 points, and the improvement of points is <30%. Total effective rate = (healed + markedly + effective)/total number of cases × 100%.

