#### Diagnostic criteria

2.2.1

Western medicine diagnosis refers to “Chinese Urological Disease Diagnosis and Treatment Guide” and “Urinary Surgery” in ED-related diagnostic standards. The diagnosis of TCM refers to the “Guiding Principles for Clinical Research of New Chinese Medicines,” and the syndrome is identified as damp-heat-stasis syndrome type. Western medicine standards refer to the “Guide to the Diagnosis and Treatment of Integrated Chinese and Western Medicine of Chinese Cerebral Infarction” by the Chinese Society of Integrated Traditional Chinese and Western Medicine. Traditional Chinese Medicine refers to the “Stroke Diagnosis and Efficacy Evaluation Standards” formulated by the Chinese Medicine Administration's Encephalopathy Acute Scientific Research Collaboration.

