#### Inclusion criteria

2.2.2

This study will be conducted in China. Patients will be recruited from urology/neurology departments of Dongzhimen Hospital Affiliated to Beijing University of Chinese Medicine. We will enroll participants based on the following inclusion criteria:

1.Those who meet the western medical diagnostic criteria for impotence (ED) and occur after stroke;2.20 ≤ age ≤ 60 years old male, normal sexual desire;3.The vital signs are stable and the stroke recovers;4.All are first stroke.5.Accept and sign the informed consent

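### The IIEF-5 responder rule asks for a gain of 1 to 5 points depending on where a man starts, and the planned chi-square ignores that baseline

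*Protocol article*

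**What the plan says.** Protocol article, section 2.4.1 (Primary outcome measures), grades each man on his IIEF-5 score after treatment:

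- Recovery: "Recovery: IIEF-5 score ≥22 points after treatment". No change from baseline is required.
- Significant effect: "IIEF-5 score < 22 points after treatment, points improved ≥60" per cent.
- Effective: final score below 22 and "The improvement of points is between 30% and 60" per cent.
- Ineffective: "IIEF-5 points after treatment are <22 points, and the improvement of points is <30" per cent.

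The first three grades are pooled: "Total effective rate = (healed + markedly + effective)/total number of cases × 100". Section 2.5 sizes the trial on this rate, 0.80 against 0.50.

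On entry, section 2.2.2 requires "Those who meet the western medical diagnostic criteria for impotence (ED) and occur after stroke", and section 2.2.1 takes the diagnosis from outside sources: "Western medicine diagnosis refers to “Chinese Urological Disease Diagnosis and Treatment Guide” and “Urinary Surgery” in ED-related diagnostic standards". No IIEF-5 value is printed there or among the exclusions in 2.2.3. The abstract specifies simple randomisation and assessment at week 8. Section 2.7 compares count data by a chi-square test and mentions no baseline adjustment.

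**The concern.** The rule mixes an absolute threshold with a relative gain, so the same improvement in points is a success for one man and a failure for another. The bar is low at both ends of the range and highest in the middle. Near 21, ordinary fluctuation is enough to succeed. At 14-17, a real gain of 3 or 4 points counts for nothing.

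Three things are at stake. The rates of 0.80 and 0.50 have no fixed meaning without a baseline mix, and section 2.5 gives none. The unadjusted test leaves baseline-driven variation in the error. And because the recovery grade has no change condition while eligibility is not tied to the IIEF-5, the endpoint does not by its own terms exclude a man who starts at or above the threshold.

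**Working it through.** **Plan's own figure.** With P1 = 0.80, P2 = 0.50 and the multiplier 10.5, n = 10.5 × (0.8×0.2 + 0.5×0.5) / 0.30² = 47.8, that is 48 per arm. This reproduces the stated 48, to which the protocol adds 5 to reach 53. The expression printed in section 2.5 does not itself yield 48. That is a separate matter and does not affect this point.

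**Minimum gain.** Assumptions: the percentage gain is relative to baseline, scores are whole numbers, and the scale runs from 5 to 25 (the article states neither the denominator nor the range). For baseline b below 22 the required gain is min(ceil(0.30 × b), 22 − b). From 22 upwards it is 0.

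| Baseline IIEF-5 | Points needed |
|---|---|
| 5-6 | 2 |
| 7-10 | 3 |
| 11-13 | 4 |
| 14-17 | 5 |
| 18 | 4 |
| 19 | 3 |
| 20 | 2 |
| 21 | 1 |
| 22-25 | 0 |

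If scores down to 1 are allowed, baselines 1-3 need 1 point and 4 needs 2, so the range is still 1 to 5.

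Worked cases: 21 to 22 is a gain of 1 point, graded as recovery. 15 to 19 is a gain of 4/15 = 26.7%, graded as ineffective. Two grades also become unreachable. From 14, a 60% gain means 14 × 1.6 = 22.4, which is no longer below 22. From 17, a 30% gain means 17 × 1.3 = 22.1, likewise.

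**Responder probability by baseline.** Assume the same normally distributed change at every baseline, with a half-point correction: P = 1 − Φ((needed − 0.5 − mean)/SD).

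| Assumed mean, SD | b = 5-6 | b = 12 | b = 14-17 | b = 20 | b = 21 |
|---|---|---|---|---|---|
| 0, 3 | 31% | 12% | 7% | 31% | 43% |
| 2, 3 | 57% | 31% | 20% | 57% | 69% |
| 3, 4 | 65% | 45% | 35% | 65% | 73% |

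Between men with the same expected change, the spread is 69 − 20 = 49 points in the second row and 73 − 35 = 38 points in the third.

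**What this does to the arm comparison.** Let p(b) be the probability above, V_b its variance over the baseline distribution, and p̄ its mean. With n = 53 per arm, the standard error from baseline imbalance is √(2V_b/n), and the total standard error is √(2p̄(1−p̄)/n).

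Example: baselines uniform on 5-21 (assumed), mean change 2, SD 3. The numbers of baseline values needing 1, 2, 3, 4 and 5 points are 1, 3, 5, 4 and 4, so

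p̄ = (1×0.691 + 3×0.566 + 5×0.434 + 4×0.309 + 4×0.202)/17 = 0.388, and V_b = 0.0212.

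- Imbalance: √(2×0.0212/53) = 0.028
- Total: √(2×0.388×0.612/53) = 0.095
- Share of responder variance: 0.0212/0.2375 = 8.9%

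Over three assumed baseline distributions on 5-21 (uniform; normal with mean 12, SD 4; normal with mean 15, SD 4):

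| Assumed mean, SD of change | Imbalance SE (points) | Total SE (points) | Share of variance |
|---|---|---|---|
| 2, 3 | 2.2-2.8 | 9.0-9.5 | 6-9% |
| 3, 4 | 1.8-2.2 | 9.7 | 3-5% |

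Removing 3-9% of the variance shortens the standard error by a factor of √0.97 = 0.985 to √0.91 = 0.954, that is by about 1.5-5%.

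**The case against.** The strongest reply is that randomisation already deals with this. Chance imbalance in baseline is part of the variability that the chi-square test allows for, so there is no systematic bias between arms and no inflated type I error. That stands. A reader might set the 38-49 point spread against the 30-point design difference and infer that baseline could create the trial's result. The documents do not support this. The spread is between individual men at different baselines, while the 30 points is a difference between randomised arms, where imbalance contributes an SE of only about 2-3 points.

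A reader might also infer that unchanged men will be counted as recovered. That is only a possibility. Entry needs an ED diagnosis under guides that are not shown and may carry their own cut-off, and a man at the protocol's recovery level would seldom be diagnosed with ED.

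The percentages rest on an assumed common change in points. If gains scale with baseline, the low-end peak shrinks. For example, with a mean change of 15% of baseline and SD 3 (assumed), P is 1 − Φ((1.5 − 0.75)/3) = 40% at baseline 5, 1 − Φ((4.5 − 2.1)/3) = 21% at 14 and 1 − Φ((0.5 − 3.15)/3) = 81% at 21. The upper-end contrast remains. The table of points needed does not rest on any change model.

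Finally, adjustment and supporting analyses are often left to an analysis plan, and graded relative gain is a design choice. Both are fair. But the responder rule and the unadjusted test are stated in the article, and the unevenness follows from that rule. Adjusting the responder comparison does not level the bar; only an analysis of the score itself does.

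**Conclusion.** The point holds as one of interpretation and precision. The required gain runs from 1 to 5 points with baseline, exactly as the rule is written, given baseline as the denominator and whole-number scores. The comparison between arms stays valid. The precision cost is modest: about 3-9% of responder variance, with an imbalance SE of about 2-3 points against a total of 9-10, under assumed change models and baseline distributions. The larger cost is that the effective rate cannot be read as a measure of benefit without knowing the baseline mix. Whether anyone could enter at 22 or more cannot be settled from the article; the printed criteria do not exclude it.

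**What to change.** - Keep the total effective rate, but replace the unadjusted chi-square with a comparison adjusted for baseline IIEF-5 in categories or by a spline (logistic model, standardised risk difference). A straight-line term would miss a relation that falls and then rises.
- Report beside it the between-arm difference in week-8 IIEF-5 adjusted for baseline (ANCOVA). This uses the whole change and does not depend on the uneven bar.
- State that percentage gain is relative to baseline, if that is what is meant.
- Reconcile eligibility with the endpoint, so that a man already at the protocol's own recovery threshold of 22 at baseline cannot be counted as a responder.

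Cost: slightly more analysis work and a clarification of eligibility or of the endpoint. The baseline score is already needed to compute percentage gain, so no new data are collected, and section 4 says recruitment has not started.
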